#### Main study

Subjects who are eligible and willing to participate in the main study will complete a standardized, validated, interviewer administered questionnaire designed to collect general demographics and evaluate factors that have been demonstrated in prospective observational studies to influence levels of bone turnover markers, BMD, and fracture risk [27]. The questionnaire will also assess total daily calcium and vitamin D intake using a modified version of the Block questionnaire. All subjects will be instructed to take the nitrate, identified in the pilot study to be the best tolerated, daily for one week. Subjects who do not develop headaches during the nitrate run-in phase will enter the main trial. The first 3 months of the main trial consist of a calcium and vitamin D pre-treatment phase. We will determine the total daily calcium and vitamin D intake from questionnaire and we will provide calcium carbonate in 500 mg tablets and vitamin D in 400 IU tablets as needed so that the total daily calcium intake for all study subjects will be 1500 mg and the vitamin D intake will be 800 IU; these are the intakes recommended in the recently published guidelines for the prevention and treatment of OP in Canada [70]. Calcium and vitamin D are the mainstay of all treatment regimens for OP and any new agent should be evaluated to assess the additional benefit it would provide. The three month calcium and vitamin D pre-treatment phase will limit any carryover effects of nitrates from the nitrate run-in phase. Further, by providing calcium and vitamin D, we hope to discourage subjects who, after being enrolled in an "OP trial", start taking additional, unreported calcium and vitamin D (co-intervention). Calcium and vitamin D will be prepared and packaged by the study pharmacist, and instructions on how to take the supplements and the PI's office number will be printed on each bottle. Subjects will be given standard verbal instructions by the PI and reminded to take the calcium and vitamin D daily with the morning meal.

All subjects who return to the study centre at three months will undergo pQCT assessments, have blood and urine taken for measurement of bone turnover markers, and be randomly assigned to placebo or active treatment. Subjects will receive a 3 month supply of study medication, calcium, and vitamin D, and will receive standard verbal and written instructions on how to take the medication, calcium, and vitamin D. At 3 months post randomization, subjects will return to the study centre and provide blood and urine samples for bone turnover markers; unused calcium, vitamin D, and study medication will be collected and counted, and subjects will be given a nine month supply of study medication, calcium, and vitamin D. At 12 and 24 months post randomization, subjects will visit the study centre and provide blood and urine samples for bone turnover markers; the unused calcium, vitamin D and study medication will be counted (at the 12 month post randomization visit we will provide a 12 month supply of calcium, vitamin D and study medication) and we will obtain BMD and pQCT assessments (Figure. 3).

### 2.3 Study subjects

The pilot and main study have identical inclusion and exclusion criteria.

#### Inclusion criteria

1. Women aged 50 and older. 2. Lumbar spine BMD (L1 to L4) T score between 0 and -2.0. 3. ≥ 3 years postmenopausal.

#### Exclusion criteria

1. Prior low trauma hip or vertebral fracture; these subjects have OP and require treatment. 2. Total hip or femoral neck T score of < -2.0; these subjects either have OP and require treatment, or are at increased risk of developing OP over the course of the main study. 3. Bone disorders other than osteopenia (e.g. hyperparathyroidism or Paget's disease); these subjects require treatment. 4. Treatment within six months of study entry with androgen, calcitonin, estrogen, progesterone, fluoride in a tablet form, raloxifene, tamoxifen, etidronate, prednisone or an equivalent at 5 mg/d for 12 months or greater, lithium or anticonvulsants. These agents can alter levels of bone turnover markers for up to six months. 5. Alendronate or risedronate use for at least four weeks, within the last three years. These agents may influence bone remodeling for up to three years. 6. Current treatment with nitrates. 7. Systolic blood pressure of ≤ 100 mm Hg or diastolic blood pressure ≥ 110 mm Hg at the baseline screening examination. 8. Abnormal ECG at the baseline screening examination. 9. History of myocardial infarction, angina, valvular or congenital heart disease. 10. Disabling conditions that may interfere with follow-up visits. 11. Inability to give informed consent. 12. Migraine headaches; nitrates can exacerbate migraines. 13. Hypersensitivity to nitrates.

### 2.4 Study outcomes

#### Pilot study

The primary outcome will be mean headache score associated with each of intermittent NTG and ISMO use. Subjects will be given four seven day diaries, with a VAS for each day of both treatment periods and the wash out period. Subjects will rate their headache upon awakening on a daily basis; our previous study demonstrated that subjects randomized to ISMO who developed headaches reported that the headache was most severe upon awakening and gradually subsided over the day [43]. The VAS uses a 100 mm continuous horizontal line with the left pole labeled "no headache" and the right pole labeled "terrible headache"; subjects will be instructed to draw a vertical line intersecting the VAS indicating the severity of their morning headache. We will calculate the mean headache score with intermittent NTG and intermittent ISMO for each subject. Then we will calculate the mean headache score for all subjects when taking ISMO and when taking NTG. The nitrate that gives the lowest mean headache score will be used in our main study. Our earlier work indicates that the nitrate formulation associated with the most severe headaches will result in the greatest number of drop outs [30]. The VAS can detect subtle changes in subjective complaints (i.e. headache), has documented reliability, and has been used in several studies designed to study the effects of NTG ointment on headache in healthy women [56,57].

#### Main study

The primary outcome will be the change from baseline in BMD at the lumbar spine over 24 months among women randomized to treatment compared with women randomized to placebo. BMD will be measured (on the same machine in all subjects) at the lumbar spine (L1 to L4) using a Lunar DPX-L bone densitometer (Lunar Corporation, Madison WI). A single experienced technician, certified by the International Society of Clinical Densitometry (ISCD) and blinded to the treatment assignment, will perform all BMD measurements. The intraclass correlation coefficient for BMD measurements is 0.98 [72]. The PI will be blinded to treatment assignment and will report the BMD. BMD reporting is objective and based on standard ISCD criteria.

We will assess four secondary outcomes in the main study:

##### 1. Change from baseline in total hip BMD

This will provide information about the effects of nitrates on cortical and trabecular bone and ultimately on the ability of nitrates to prevent hip fractures.

##### 2. Change from baseline in bone formation and bone resorption markers

Measuring markers of bone turnover will increase our understanding of the mechanisms by which intermittent nitrates increase BMD (i.e. a decrease in bone resorption and/or an increase in bone formation). We will measure bone turnover markers three months after initiating calcium and vitamin D because we expect a 10% decrease in markers with the use of supplements, and the maximal change in bone markers is typically observed at three months [36]. Thus, we will be assessing any additional effects of intermittent nitrates on markers of bone turnover in women receiving calcium and vitamin D supplements. Urinary NTx will be measured on a second morning urine sample using a monoclonal antibody technique (Osteomark) [73]. The intra-assay variability is 7.6% and the inter-assay variability is 4.0%. Serum BSAP will be measured on a fasting serum sample using a monoclonal antibody technique (Metra Biosystems) [74]. The intra-assay variability is 5.8% and the inter-assay variability is 5.2%. To minimize variability, subjects will be given written and verbal instructions on how to collect the second morning urine sample; for each subject we will collect all the samples (baseline, three, 12 and 24 month post randomization) at the same time, and we will store the blood and urine at -70°C and analyze all the samples together in a single laboratory. We will compare measures of bone turnover markers at 3, 12, and 24 months after randomization using a repeated measure of analysis of variance [75]. By measuring markers at three months we will be able to directly compare these results to the findings in our earlier study. By measuring markers at 12 and 24 months we will be able to evaluate to a limited degree, the question of tachyphylaxis with nitrates. Recall that in our earlier study we found a decrease in markers of bone resorption and an increase in markers of bone formation after 90 days of treatment with intermittent ISMO [30,31]. Measuring markers after one and two years of treatment will allow us to determine if there is still a marked decrease in bone resorption and increase in bone formation; no further changes in markers may indicate that the effects of nitrates on bone is transient.

##### 3. Adverse events

Adverse events will be assessed using a standardized, validated interviewer administered questionnaire on a monthly basis by telephone.

##### 4. Bone microarchitecture

Fracture risk is influenced by both the quantity of bone (assessed by BMD) and quality of bone. Fracture risk is influenced by both the quantity of bone (assessed by BMD) and quality of bone. Indeed, recent reports suggest that up to 40% of fracture risk is explained by decreases in bone quality [5,62]. Our results indicate that nitrates increase bone formation. Exercise and agents, such as PTH, that form bone add bone to the periosteal surface of cortical bone; this may also apply to nitrates. Small increases in the external diameter of bone substantially increase the bending strength of long bones. Unfortunately, bone density by DXA of the complex structures of hip and spine have poor resolution of cortical bone edges and cannot accurately measure the periosteal accretion of cortical bone. In fact, addition of periosteal bone will increase the diameter and, therefore, the projected area of a bone. Since BMD is calculated as total bone mineral content divided by bone area, an increase in bone diameter may paradoxically tend to decrease BMD! Therefore, it is essential to use a measurement that precisely measures cortical dimensions in tubular bone.

Cross-sectional moment of inertia is one of the best biomechanical measurements of the strength of long bones. Trabecular density also contributes to the strength of many bones with high trabecular content. All of these features can be measured with pQCT [66]. PQCT measures are precise, with a minimum detectable change for volumetric bone density of 0.03 g cm^-3 ^[67,68]. PQCT measurements of volumetric bone density and trabecular bone texture have been used by researchers at McMaster University to demonstrate that reductions in fracture risk induced by hormone replacement therapy are due to deposition of bone at the endocortical surface [67]. Statistically significant responses in density, area and texture were detected within six months when 21 women starting therapy were compared with 32 matched controls. Previous work at McMaster was performed with a second generation pQCT machine. The investigators at McMaster have recently obtained a third generation scanner (Stratec XCT2000) that allows measurements of greater reproducibility in both the radius (nonweight bearing) and the tibia (weight bearing). This is particularly relevant with regard to NO as in vitro studies demonstrate that the nitric oxide synthase gene promoter is activated in response to shear stress (equivalent to weight bearing in humans) [68]. Thus, increased levels of NO that results in decreased bone resorption may be one mechanism by which weight bearing prevents bone loss. Our study will test this hypothesis by comparing pQCT measurements in the radius (nonweight bearing) and tibia (weight bearing) among women randomized to nitrates and placebo.

### 2.5 Sample size

#### Pilot study

We wish to detect at least 15 units difference in headache score using the VAS between the intermittent NTG and ISMO groups, which is consistent with a modest effect [57]. We assumed a power of 90% and two sided alpha of 0.05, a standard deviation of 27.78 (based on studies using the VAS to report headaches in healthy women), [56,57] and a small correlation of 0.5 among the repeated measurements [77]. Based on these assumptions, the number of subjects needed for comparing (paired) the mean headache scores for two groups is 20 subjects (Table 4A). We will increase this number by 10%, to account for women who develop headaches that continue into the washout period and cannot go on to the second treatment. Note that this is a conservative approach, in our earlier study all women who developed headaches reported that when they stopped the treatment the headache resolved within 24 hours. Based on these assumptions, we will require 22 subjects for our pilot study.

**Table 4A T4:** Formula used for sample size calculation for pilot study.

*n *= (*Z*_1-*α*/2 _+ *Z*_1-*β*_)^2 ^{1 + (*n *- 1)*ρ*}/(*n*Δ^2^), where *n *= 7, *ρ *= 0.2, Δ = , *β *= 0.1.

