#### 2.1.2 The pilot study and nitrate run-in phase

No published studies compare nitrate preparations with respect to the frequency and severity of headaches. In our earlier study, 16 of the 96 (17%) women randomized to ISMO dropped out due to headaches compared with 2 of 48 (4%) women in the placebo [30,31]. All the women in the ISMO group who dropped out due to headaches did so within two days of randomization. The severity of the headaches determined drop out such that a woman with one day of severe headache was five times more likely to drop out than a woman with mild headaches for several days. Headaches were most severe upon awakening and subsided over the day. All headaches resolved within 24 hours of discontinuing the treatment assignment.

In the open label trial discussed earlier women were given 15 mg/day of NTG ointment and no headaches were reported [42]. Although cross-trial comparisons are problematic, this difference suggests that NTG ointment is better tolerated than oral ISMO. One explanation relates to differences in pharmacokinetics; compared with NTG ointment, ISMO results in a much longer exposure to NO [54-57]. Alternative explanations relate to differences in subjects (the open label trial studied young women with surgical menopause who had hot flashes, while we studied healthy older postmenopausal women), or in ascertainment of adverse events (the open label trial relied on self-report whereas we regularly inquired about headaches). Because there is considerable uncertainty about the relationship of nitrate preparation and headaches, our pilot study will focus on which of NTG or ISMO gives the least headaches.

To minimize differential drop out the main trial will be preceded by a one week nitrate run-in phase. All women eligible and willing to enter the trial will be instructed to take the nitrate, identified in the pilot as the best tolerated, for one week (as noted above women who develop headaches do so within 48 hours of taking the drug). Women who do not develop headaches will enter the main trial and, after 3 months of calcium and vitamin D (pre-treatment phase), will be randomized to placebo or treatment.

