#### 2.1.3 The intervention: rationale for the nitrate preparation, dose, and frequency of administration

Although several other forms of nitrates (e.g. transdermal patch, sublingual sprays) are available, we chose to study NTG ointment (15 mg/day) and oral ISMO (20 mg/day) because these are the only agents for which data on the safety and tolerability in healthy postmenopausal women exist. Moreover, the only studies that have reported changes in bone turnover markers have used either NTG ointment or ISMO. We will study the 20 mg dose of ISMO as our earlier work found that this dose was associated with the greatest change in bone turnover markers [30,31]. There was no difference in headache incidence among women randomized to 5 mg compared to 20 mg. The 20 mg dose is marketed and readily available; this will be important if we use ISMO in a RCT of nitrates for fracture prevention.

We will study the 15 mg/day dose of NTG ointment. This dose was used in the open label trial of NTG for the prevention of oophorectomy induced bone loss [42]. The 15 mg/day dose was based on dose response studies in rodents: a dose of 0.2 mg/kg/day of NTG was associated with the greatest change in bone turnover markers [25,29,58].

We considered using the NTG patch instead of NTG ointment. The NTG patch has a major disadvantage: it has a long (24 hour) average duration of action and, therefore, may cause tachyphylaxis to the bone effects of nitrate. In contrast, the ointment has a much shorter (6 hour) average duration of action so that once daily administration avoids development of tachyphylaxis. We recognize that ointment is more difficult to apply than a transdermal patch and might stain clothing. However, we have used the ointment in 18 women in our pilot study with no mention by women of messiness or staining of clothes.

We will administer both NTG and ISMO once a day i.e. intermittently. While other dosing frequencies may increase BMD (e.g. continuous dosing, or even once weekly dosing), data from both the cardiovascular literature and our observational study suggest that too frequent dosing (e.g. ISMO 20 mg twice a day or NTG every eight hours) is associated with tachyphylaxis while pharmacologic studies suggest that too infrequent dosing (e.g. less than once a day) results in increased frequency and severity of headaches. Thus, once daily or intermittent administration of nitrates will give the greatest change in BMD and the fewest headaches.

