### 2.2 Trial interventions

#### Pilot study

Subjects will receive NTG ointment; at 15 mg/day (one inch of 2% ointment applied to the upper arm) for one week and ISMO at 20 mg/day for one week. The order of treatments will be randomized. In between each treatment there will be a two week washout. The washout exceeds ten half lives of NTG (one hour) and ISMO (five hours) and will eliminate any carryover effects [54-57]. Subjects who report headaches during the wash out will be excluded from the second treatment phase and considered as drop outs in our analysis. We have considered drop outs in our sample size calculations. Both treatments will be administered with placebo (tablet or paste, as appropriate). Subjects will receive standard instructions on how to take the tablet (at bed time with a glass of water; as was given in our earlier study) and patch (apply it first thing in the morning; as was given in the earlier study).

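### The pilot's 10% allowance covers only headaches that persist into the washout, not the plan's own 17% early ISMO drop-out, so the 20 complete pairs behind the stated 90% power are not secured

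*Protocol article*

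**What the plan says.** All places are in the protocol article.

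- **Size (section 2.5, Pilot study).** "We wish to detect at least 15 units difference in headache score using the VAS", with "a standard deviation of 27.78" and "a small correlation of 0.5 among the repeated measurements". On error rates: "We assumed a power of 90% and two sided alpha of 0.05". The result is 20 paired subjects.
- **Allowance (same section).** "We will increase this number by 10%, to account for women who develop headaches that continue into the washout period". This gives 22 women. It is called conservative because, in the earlier trial, headaches cleared within 24 hours of stopping.
- **Assurance (section 2.2, Pilot study).** After stating that women with headache in the washout do not go on to the second treatment: "We have considered drop outs in our sample size calculations".
- **Drop-out on ISMO (section 2.1.2).** In the earlier trial "16 of the 96 (17%) women randomized to ISMO dropped out due to headaches", all of them within two days of randomization.
- **Use of that rate elsewhere.** Section 2.1 and the main-study part of section 2.5 apply 17% to the one-week nitrate run-in.
- **Design and test (sections 2.1 and 2.6).** Each pilot woman takes both nitrates for one week each, in random order. The comparison is a paired t test.

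**The concern.** A paired test needs usable data on both nitrates from each woman. The plan's own experience is that about one woman in six stops ISMO for headache, and that this happens so early that a one-week exposure carries the whole risk. The plan builds the rate into the main-study run-in but not into the pilot, where every woman is exposed to ISMO.

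The argument for calling the 10% conservative is that headaches resolve within 24 hours of stopping. That concerns how long a headache lasts, not whether a woman leaves treatment. The 16 women who dropped out did so although all headaches resolved that quickly.

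Two things are at stake. One is the stated size and power of the study that selects the main-study drug. The other is which women are missing: section 2.1.2 ties drop-out to severe headache, so lost or truncated ISMO weeks would come mainly from the women most affected, which would tend to understate ISMO headache.

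**Working it through.** **Inputs.** Difference 15, SD 27.78, two-sided alpha 0.05, power 90%, correlation 0.5 (text) or 0.2 (Table 4A), 7 daily scores (Table 4A), and 22 women, all from section 2.5. ISMO headache drop-out is 16/96 = 0.167 (section 2.1.2). Drop-out on NTG is taken as zero.

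**1. Reproducing the plan's figure.** Table 4A: N = (z for 1−α/2 + z for 1−β)² × {1 + (7 − 1)ρ} / (7 × Δ²), with Δ = 15/27.78 = 0.540 and squared z-sum 10.507.
- ρ = 0.5: 10.507 × 4 / (7 × 0.2916) = 20.6, in line with the stated 20.
- ρ = 0.2, as printed in Table 4A: 10.507 × 2.2 / (7 × 0.2916) = 11.3, which does not match 20.
- 20 × 1.10 = 22, as stated.

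**2. Expected complete pairs from 22 women.**
- Reading A, every ISMO stop loses the pair: 22 × (1 − 16/96) = 18.3. The binomial chance of at least 20 pairs is 0.27.
- Reading B, only women given ISMO first lose the pair when they stop. About half the women are in that order, so the loss is 22 × 1/2 × 16/96 = 1.8, leaving 20.2. The chance of at least 20 pairs is 0.72.

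**3. Power on the plan's formula with ρ = 0.5.** Power = Φ(3.2415 × √(N/20.6) − 1.96).

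| Complete pairs | Power |
|---|---|
| 18.3 (reading A) | 86.4% |
| 20 (plan) | 89.2% |
| 20.2 (reading B) | about 89% |
| 22 (no loss) | 91.8% |

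**4. Sensitivity.** With a t rather than a normal reference, power is 85.8% at 20 pairs and 81.5% at 18, so the drop is of similar size from a lower start. With Table 4A's ρ = 0.2, 18 pairs would still have about 98%.

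**The case against.** The strongest reply is that the article never says a woman who stops ISMO early is lost to the paired comparison. The outcome is a mean of daily diary scores, so she may have some ISMO scores. Her headache should clear within a day, so the washout exclusion need not apply to her. If she took NTG first, her NTG week is already complete. How partial diaries are scored may be set out in a full plan that is not shown. This stands, and it is why a flat statement that 22 women cannot give 20 pairs would go too far. If no early stop cost a pair, all 22 could contribute. It does not remove the inconsistency: even on reading B the two-woman margin is used up by ISMO stops, leaving nothing for the washout exclusions it was meant to cover.

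Other points that stand:
- The 10% is defensible for the event it names.
- Section 2.4 selects the nitrate with the lowest mean score, so a few points of power do not decide the drug. Section 3.0 reports the pilot complete, with significantly lower headaches on NTG.
- The 17% pools the 5 mg and 20 mg groups. Section 1.4 reports similar headache frequency in both but does not give drop-out by dose.

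Two stronger readings are tempting and not supported. A reader might take a further 10% off the 18.3 pairs, giving 22 × (1 − 16/96) × 0.9 = 16.5. But the 10% is an allowance, not an observed rate, and both losses draw on the same women with ISMO headache. A reader might also see a shortfall in section 2.1.3, which says "we have used the ointment in 18 women in our pilot study". Women given NTG first would have used the ointment whatever happened later on ISMO, so even if every ISMO-first stop ended participation, about 20 users would be expected. The figure shows nothing about complete pairs.

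**Conclusion.** The point holds as an unaddressed source of loss, not as an arithmetic error: 20 × 1.10 is 22, and the 20 reproduces. The allowance leaves out the 17% on-treatment drop-out that the plan applies to the same length of nitrate exposure elsewhere, so the general assurance in section 2.2 is not borne out for the pilot.

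The size is modest. About 18 to 20 complete pairs are expected, with power about 86% to 89%, against a claim of 90% with a conservative margin. This assumes that the earlier trial's 16/96 carries over to the pilot, that the loss lies between readings A and B, that NTG causes no drop-outs, and that ρ is 0.5. The last matters most: Table 4A prints 0.2, and until the two are reconciled no power figure for the pilot is firm.

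**What to change.** In section 2.5, Pilot study:
- Limit the word conservative to the washout allowance.
- Acknowledge on-treatment ISMO headache drop-out at 17%, citing section 2.1.2, and align the assurance in section 2.2 with it.
- Reconcile the correlation in the text with Table 4A. If 0.5 is confirmed, state about 18 to 20 expected complete pairs and power of about 86% to 89%; otherwise recompute.
- State how women who stop ISMO early enter the paired comparison, including how a partial diary week is scored.

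With the pilot result, report the number of complete pairs and the headache drop-outs on each nitrate.

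The cost is a few sentences and one line of reporting. The stated power becomes slightly less favourable. No extra patients are needed.
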